## Abstract

**Rationale:**

Delirium is defined as acute organic brain dysfunction characterised by inattention and disturbance of cognition. It is common in the intensive care unit and is associated with poorer outcomes. Good quality sleep is important in the prevention and management of delirium. Melatonin is a natural hormone secreted by the pineal gland which helps in the regulation of the sleep-wake cycle. It is possible that melatonin supplementation in intensive care improves sleep and prevents delirium.

**Methods and design:**

The ‘Prophylactic Melatonin for Delirium in Intensive Care’ study is a multi-centre, randomised, double-blinded, placebo-controlled trial. The primary objective of this study is to determine whether melatonin given prophylactically decreases delirium in critically ill patients. A total of 850 ICU patients have been randomised (1:1) to receive either melatonin or a placebo. Participants were monitored twice daily for symptoms of delirium.

**Results:**

This paper and the attached additional files describe the statistical analysis plan (SAP) for the trial. The SAP has been developed and submitted for publication before the database has been locked and before the treatment allocation has been unblinded. The SAP contains details of analyses to be undertaken, which will be reported in the primary and secondary publications.

**Discussion:**

The SAP details the analyses that will be done to avoid bias coming from knowledge of the results in advance. This trial will determine whether prophylactic melatonin administered to intensive care unit patients helps decrease the rate and the severity of delirium.

**Trial registration:**

Australian and New Zealand Clinical Trial Registry (ANZCTR) ACTRN1261600043647, registration date: 06 April 2016. WHO Trial Number – U1111-1175-1814

## Introduction

Delirium is a condition of acute organic brain dysfunction with disturbances of attention and cognition, a fluctuating course, and occurring as a direct consequence of an underlying medical condition [1]. It is particularly common in patients in intensive care units (ICU), with a wide range of prevalence reported in the literature (11–80%) [2–4]. Delirium in ICU is associated with poorer outcomes, including higher mortality, more time on a ventilator, increased length of stay (LOS), greater post-operative complications, increased need for tracheostomy, increased medical costs, and higher risk of dementia and cognitive impairment [3, 5–12].

Good quality sleep at night is recognised as an important aspect in the prevention and management of delirium. Melatonin is a natural hormone secreted by the pineal gland, which helps in the regulation of the sleep-wake cycle. Decreased melatonin levels and fluctuations in its metabolite, 6-SMT, have been associated with delirium in post-surgical and intensive care patients [13, 14].

It is possible that supplementing melatonin improves sleep and prevents delirium. A number of clinical trials of melatonin or melatonin agonists for the prevention of delirium have been performed to date [15–26]. It is difficult to draw firm conclusions due to conflicting results, methodological issues, and patient heterogeneity.

The ‘Prophylactic Melatonin for Delirium in Intensive Care’ is a multi-centre randomised double-blinded, placebo-controlled trial. The primary objective of this study is to determine whether melatonin given prophylactically decreases delirium in critically ill patients.

This study may provide evidence for a simple and effective agent to reduce delirium in patients admitted to the ICU.

## Study methods

This is a multi-centre, randomised, double-blinded, placebo-controlled trial of melatonin versus placebo to decrease the rate of delirium in ICU. A total of 850 ICU patients have been randomised on a 1:1 ratio to receive either melatonin or a placebo. Study participants were administered an oral dose of melatonin 4 mg enterally or placebo once daily at 21:00hs. for up to 14 days or until discharge from the ICU. Participants were monitored twice daily for symptoms of delirium. Additionally, data is being collected on the duration and severity of delirium, sleep quality, hospital and ICU length of stay (LOS), duration of mechanical ventilation, and mortality.

Patients were randomised according to a computer-generated randomisation list, stratified by site, with standard block sizes of 6. Variable block sizes were considered unlikely to provide additional benefit, as the study drug and placebo have the same appearance and all clinical staff are blinded, thus maintaining allocation concealment. The randomisation list has been maintained by the University of Western Australia Centre for Applied Statistics.

The patients, investigators, ICU doctors, and nurses looking after patients enrolled in the study are blinded to the treatment that the patients are receiving. Only the University of Western Australia Centre for Applied Statistics, the compounding pharmacy, and the independent Data Safety Monitoring Committee (DSMC) (should they need to, in order to investigate an adverse event) have had access to the treatment allocation list.

Based on the sample size calculations, with an alpha value of 0.05 and a power of 80%, a total of 850 patients have been recruited to the study, with 425 patients in each arm. Estimates of sample size were made based on the percentage of delirium-free assessments (the primary outcome) and, secondarily, the ICU LOS. LOS was chosen in addition to the percentage of delirium-free assessments as a significant relationship between delirium and LOS has been observed. Delirium assessment is by its nature subjective and the investigators wished to also allow the study to be powered to detect a reduction of LOS of 1 day (as an objective patient-orientated outcome). An audit of 100 patients across the two primary sites was used to provide preliminary data to guide sample size calculations where an average of 54% of assessments were deemed delirium free (standard deviation of ± 45%). The research group is interested in being able to detect a 10% increase in the percentage of delirium-free assessments. This would require a sample size calculation of 319 per group. Adjustment for non-parametric data (15%) increases this to 367 per group. It is expected that up to 10% of patients recruited in the study will not be assessable for delirium at any point during the study. To account for this, and missing data/loss to follow-up, the sample size was increased by 15% to 423 patients per group (total rounded to 850).

To detect a change in LOS of 1 day, using a sample size calculation for a gamma distribution, 387 patients per group would be required. The greater number of 850 was selected to have enough power to answer both questions. The formula used to calculate sample size was that described by Wand and Chow in 2007 [27].

The framework of the study is of superiority of melatonin over placebo for the prevention of delirium. Superiority analyses will be two-sided and considered statistically significant at the 5% level.

The DSMC is comprised of an independent intensivist, an epidemiologist, and a statistician independent of the trial statistician. The independent DSMC will review all serious adverse events and perform an interim analysis after 400 patients using the Haybittle-Peto stopping rule. The Haybittle-Peto stopping rule states that if an interim analysis shows a probability of equal to or less than 0.001 that a difference as extreme or more between the treatments is found, given that the null hypothesis is true, then the trial should be stopped early [28].

Statistical analysis of data will all occur collectively once all data, including follow-up at 90 days, has been collected. Outcome assessments were undertaken during ICU stay, at discharge from ICU, at discharge from hospital, and at 28 and 90 days.

## Statistical principles

Differences will be considered statistically significant when *P* values are < 0.05, and 95% confidence intervals (95% CI) will be reported.

Adherence to protocol will be considered when patients have received all the required doses while in ICU and all the CAM-ICU assessments. This will be presented with descriptive statistics as a percentage and numerator and denominator. Protocol deviation is defined as lack of compliance with study drug administration or lack of assessment with CAM-ICU. All protocol deviations will be collated and presented in the results as descriptive statistics. All analyses will be conducted on both an intention-to-treat (ITT) and per-protocol (PP) basis. The ITT sample is defined as all randomised subjects including those who are lost to follow-up or have missing data. If the patient does not receive the assigned intervention post-randomisation, the patient will still be included in the ITT sample and analysed according to assigned treatment group.

## Trial population

Screening data will be presented as descriptive statistics. Patients eligible to be considered for the study must be admitted to the ICU with an expected total LOS of at least 72 h, as determined by the treating intensivist. Eligible participants also must be able to be enrolled and treated within 48 h of being admitted to the ICU.

Exclusion criteria for participation in the study includes (1) patients aged < 18 years; (2) patients already on melatonin before their admission to ICU; (3) prior hypersensitivity reaction to any of the components of the study drug (melatonin, sucralose and glycerol, marshmallow flavour); (4) patients expected to be discharged within 72 h of their ICU admission; (5) expected/inevitable death within next 48 h; (6) pregnant or breastfeeding; (7) non-English speaking; (8) patients that are not expected to improve adequately to be able to be assessed with a CAM-ICU score during their ICU stay; (9) patients that are not able to be assessed due to neurological problems that would affect their ability to participate in a CAM-ICU assessment, as judged by treating physician; (10) no enteral route, as melatonin is not available in intravenous formulation; and (11) hepatic impairment defined as alanine transferase (ALT) > 500 IU/L, previous liver transplant, or liver cirrhosis categories Childs-Pugh B and C.

A CONSORT flow diagram will be presented. (Fig. 1) This will include the number of patients assessed for eligibility, excluded, randomised, allocated to each intervention arm, followed up, and analysed for each group. A report of withdrawals will be provided, describing the level at which they have occurred, the timing of withdrawals, and the reasons for the withdrawals.

**Fig. 1 Fig1:**
[figure not shown]
Statistical analysis plan flowchart version 1

Baseline characteristics including age, gender, severity scores, source of admission, and diagnosis will be presented as a table and summarised.

## Analysis

Primary and secondary outcomes will be analysed as described below. Where appropriate, analysis of primary and secondary outcomes will be analysed by a number of predetermined subgroups. These subgroups will include (1) percentage of delirium-free assessments by age: less than 65 or more than 65 years of age; (2) percentage of delirium-free assessments by gender; (3) percentage of delirium-free assessments by delirium subgroup at baseline: hyperactive, hypoactive, and mixed, as well as no delirium; (4) percentage of delirium-free assessments by diagnostic category (respiratory, cardiovascular, gastrointestinal, toxicological, neurological, metabolic, sepsis, trauma, traumatic brain injury); and (5) percentage of delirium-free assessments by > 50% risk or < 50% risk as per Pre-Deliric Score (calculated from first 24 h of ICU admission). Multiplicity adjustments will not be made.

For the primary outcome of percentage of delirium-free episodes, patients will be assessed for delirium twice a day for 14 days or until they are discharged from ICU, whichever occurs first. The CAM-ICU tool will be used to assess delirium, with a result recorded as either ‘positive’ or ‘negative’ for delirium. The assessment will be carried out by trained ICU medical or nursing staff. The percentage of delirium-free assessments will be calculated for each participant. The percentage of delirium-free assessments for participants in each group will then be compared using Student’s *t* test. It is assumed that the data will be normally distributed. If the distribution of the data is not normally distributed, alternative approaches will be considered; however, the initial plan is robust to deviations from normality with this sample size. Supporting analysis will use linear regression making adjustments for baseline covariates.

A secondary analysis will look at the rates of delirium in each group. The number of times an individual is reported as being positive for delirium and the total number of assessments will be examined by a comparison of rates. In addition, a Poisson regression will be used with the number of positive delirium assessments reported and offset the total number of assessments. Baseline characteristics will be included as covariates in the model. The covariates will include age, gender, delirium subtype, diagnostic category, and Pre-Deliric score.

Finally, an analysis that looks at whether the individual reported a positive delirium assessment during their stay will be undertaken by comparing proportions between the groups through a logistic regression analysis controlling for variables including age, gender and length of stay.

The secondary outcomes to be analysed include (1) severity and duration of delirium, (2) sleep quality, (3) ICU and hospital length of stay;,(4) duration of mechanical ventilation, (5) mortality, and (6) economic analysis. Each secondary outcome will be adjusted for the same covariates as mentioned before: age, gender, delirium subtype, diagnostic category, and Pre-Deliric score.

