### Mortality

Mortality (time to death) will be analysed using Kaplan-Meier curves and Cox proportional hazard models, both unadjusted and adjusting for previously described covariates. Individuals who did not experience an event (death) will be censored at the end of the follow-up period of the study. Individuals withdrawn from the study early or lost to follow-up will be censored at the date of withdrawal or the last contact visit respectively. Results will be presented using hazard ratios and 95% confidence intervals for relative comparisons between the groups and absolute risk and differences will be estimated at both 28 and 90 days.

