### Missing data

Due to the nature and implementation of the CAM-ICU tool, it is expected there will be some missing data. However, such data is expected to be missing at random and consequently appropriate analyses will be carried out. The patterns of data availability for primary and secondary outcomes and reasons for missingness, where known, will be summarised for the two treatment groups. In situations where mixed modelling is the primary analysis, missing data will be handled by the likelihood-based estimation used in these analyses where the MAR assumption holds. In other situations of missing data, analyses will be carried out, if applicable, using multiple imputation.

It is expected that the source of missing data will be predominantly the dependent variable (based on missed delirium free assessments and outcomes). Consequently, we will not use multiple imputation techniques if this is the case and simply report the missingness patterns. However, if missing data is present in other variables, we will use these techniques, utilising the multiple imputation with chained equations (MICE) methodology [31].

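### ICU death carries no weight in the primary delirium percentage or in any other planned delirium analysis, so a mortality difference between arms could shift the result in either direction

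*SAP article*

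**What the plan says.** All references are to the SAP article.

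- **Window (Analysis).** For the primary outcome, "patients will be assessed for delirium twice a day for 14 days or until they are discharged from ICU, whichever occurs first". Death is not listed as an end of the window.
- **Score (Analysis).** CAM-ICU is used "with a result recorded as either ‘positive’ or ‘negative’ for delirium", and "The percentage of delirium-free assessments will be calculated for each participant". The percentages are compared by Student's t test, with a supporting linear regression on the same percentage.
- **Eligibility (Trial population).** The only exclusion that concerns death is "expected/inevitable death within next 48 h". Later ICU deaths inside the 14-day window can therefore occur.
- **Missing data.** For missing CAM-ICU results, "such data is expected to be missing at random and consequently appropriate analyses will be carried out". If it is mainly the outcome that is missing, "we will not use multiple imputation techniques if this is the case and simply report the missingness patterns". The section does not mention death.
- **Mortality.** This is a separate secondary outcome: "Mortality (time to death) will be analysed using Kaplan-Meier curves and Cox proportional hazard models", with absolute risks and differences at 28 and 90 days. No analysis links it to the primary outcome.

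**The concern.** The percentage describes only the assessments a patient lived to have. A short, uniformly negative record cut off by death gives the best possible score. A 14-day survivor with 4 positive results in 28 scores 24/28 = 85.7% and so ranks below that patient.

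The other planned delirium analyses do not make up for this:

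- The Poisson model for positive assessments uses total assessments as its offset, so death shortens the offset.
- The ever-positive logistic model counts an early death without a positive test as no delirium.
- Delirium and coma-free days are offset by days in ICU, which death also shortens.

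At stake is the reading of the primary result. If the arms differ in ICU mortality, part of the difference in percentages could reflect who died and not who was delirious. None of the described delirium analyses would show this.

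**Working it through.** **1. The plan's own figure.** Study methods gives a mean of 54%, SD 45%, a 10-point target and 319 per group, "with an alpha value of 0.05 and a power of 80"%, two-sided. Normal approximation: 2 × (1.96 + 0.8416)² × 45² / 10² = 317.9, so 318; the t-test version gives 318.84, so 319. Then 319 × 1.15 = 366.85, so 367, and 367 × 1.15 = 422.05, so 423. The stated figures reproduce, and this point does not concern the sample size arithmetic.

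**2. One patient.** Two negative assessments a day, then death. The plan's score is negatives / completed. The alternative is negatives / 28, with slots after death counted as not delirium-free.

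| Death after day | Plan | Over 28 slots |
|---|---|---|
| 1 | 2/2 = 100% | 2/28 = 7.1% |
| 2 | 4/4 = 100% | 4/28 = 14.3% |
| 3 | 6/6 = 100% | 6/28 = 21.4% |
| 5 | 10/10 = 100% | 10/28 = 35.7% |

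A patient who dies with no completed assessment has 0/0, hence no score, and cannot enter the t test.

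**3. The arm contrast.**

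Inputs from Study methods: mean 54%, SD 45 points, and up to 10% never assessable, so 425 × 0.90 = 382 per arm.

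Assumptions not in the document: no true effect on delirium; ICU mortality 10% v 15% (or 10% v 18%); the audit mean of 54% applied to survivors; and a range of mean scores before death.

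- Shift = (difference in death proportion) × (pre-death score − 54)
- SE = 45 × √(2/382) = 3.26 points
- Chance of a significant false benefit for the arm with more deaths = 1 − Φ(1.96 − shift/SE). With no shift this is 2.5%.

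| ICU deaths | Pre-death score | Shift (points) | False benefit |
|---|---|---|---|
| 10% v 15% | 30% | 0.05 × (−24) = −1.2 | 1.0% |
| 10% v 15% | 54% | 0 | 2.5% |
| 10% v 15% | 80% | 0.05 × 26 = +1.3 | 5.9% |
| 10% v 15% | 100% | 0.05 × 46 = +2.3 | 10.5% |
| 10% v 18% | 100% | 0.08 × 46 = +3.7 | 20% |

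The sign turns at a pre-death score of 54%. In the first row the tilt favours the arm with fewer deaths, whose chance of a false benefit becomes 1 − Φ(1.96 − 1.2/3.26) = 5.6%.

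**4. The supporting score in the same scenario.** Take 10% v 15%, deaths spread evenly over days 1 to 7, and all tests before death negative. The mean score over 28 slots is then (2/28) × 4 = 28.6%, so the supporting contrast shifts by 0.05 × (28.6 − 54) = −1.3 points, where the primary shifts by +2.3. The two together show how far the conclusion depends on the handling of death.

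**5. Would a rule on claiming benefit help?** A simulation of the scenario in step 4 was used to test a rule that blocks a claim when the two estimates have opposite signs. It stopped only about 4% of false benefits at 10% v 15% and about 24% at 10% v 18%. Significance needs about 1.96 × 3.26 = 6.4 points, while the supporting estimate lies only about 3.6 points below the primary, so it usually stays positive.

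**The case against.** **Slots after death may simply lie outside the window.** A reader might infer that the plan treats assessments after death as missing at random. It does not say so. Missing data never mentions death and links missingness to the CAM-ICU tool, and Study methods places assessments during the ICU stay, which death ends. This objection stands. It changes nothing numerically: on either reading the percentage is formed from completed assessments and death has no weight.

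**A condensed article may leave the definition elsewhere.** The abstract refers to additional files that are not shown, and an explicit end-of-window rule for death could be there. The lack of that wording is therefore weak evidence on its own. What remains is that the article sets out its delirium analyses one by one, and none gives death any weight.

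**The upper figures stack assumptions.** They need a 5- or 8-point mortality difference and every patient who dies to be assessable and negative throughout. The audit mean was not restricted to survivors. This stands, so +2.3 points is a bound under 10% v 15% and not an expectation.

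**Mortality is reported.** Hazard ratios and absolute differences with intervals will let a reader see an imbalance. This is a real safeguard, although power to detect 10% v 15% with 425 per arm is only about 60%, and seeing an imbalance does not show how far it moved the primary estimate.

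**Counting death as failure is a choice of estimand.** This is so, and it is why the added analysis should be supporting only.

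**Conclusion.** The point holds in a limited form. As described, the primary percentage and all the other delirium analyses give ICU death no weight, so a mortality difference could shift the primary contrast with no effect on delirium. Under 10% v 15% ICU mortality and the other assumptions listed, the shift runs from -1.2 to +2.3 points against a 10-point target.

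A reader might infer that the design favours a false finding of benefit. The documents do not support that: they give neither ICU mortality nor results before death, and the bias reverses when patients who die score below the survivors' mean. This is a worthwhile and inexpensive improvement to the interpretation of the primary result. It does not invalidate the t test or the sample size.

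**What to change.** - Keep the t test on the percentage of delirium-free assessments as the primary analysis.
- In Analysis, state that ICU death also ends the assessment window.
- In Missing data, state that slots after death are not missing data.
- Add one pre-specified supporting analysis with the same model, in which every scheduled slot from ICU death to day 14 counts as not delirium-free.
- Report it beside the primary result, with the number of ICU deaths by day 14 in each arm.
- Use it to interpret the primary result only. Add no rule for claiming benefit: it would put a success condition on an otherwise unchanged primary analysis and would stop few false claims.

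The cost is some SAP wording and one analysis of data already collected. The article says that it was submitted before database lock and unblinding; a change made at that stage would not be informed by results. The downside is that the supporting measure mixes death with delirium and scores deaths over 28 slots but discharges over fewer. It also responds to mortality differences in its own right, so it should stay supporting.

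### The primary t test ignores the site strata and the collected baseline covariates, and carries a normality condition that the audit figures already rule out; the test is valid, but a site- and covariate-adjusted linear model would be better fixed and more precise

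*SAP article*

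**What the plan says.** **Design.** Under Study methods: "Patients were randomised according to a computer-generated randomisation list, stratified by site, with standard block sizes of 6".

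**Primary comparison.** Under Analysis, each patient's percentage of CAM-ICU assessments without delirium is compared between arms by Student's t test, with no covariates. Then: "Supporting analysis will use linear regression making adjustments for baseline covariates". That sentence does not itemise the covariates.

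**Covariate lists.** For the Poisson model of delirium rates: "The covariates will include age, gender, delirium subtype, diagnostic category, and Pre-Deliric score". The same five are repeated for the secondary outcomes. The logistic model for any positive assessment and the model for duration of ventilation have open lists, which give examples only. Site is named in none of them.

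**Distribution.** "It is assumed that the data will be normally distributed". The text goes on to say that other, unnamed methods will be considered if it is not, and in the same sentence that the t test is robust to non-normality at this sample size. Yet the sample size paragraph reports "an average of 54% of assessments were deemed delirium free (standard deviation of ± 45" percentage points) and adds 15% to the sample size for non-parametric data.

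**The concern.** There are two separate points.

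1. **Strata and covariates.** Blocking within site balances the arms on site, so differences between sites add almost nothing to the true variance of the treatment difference. An analysis that omits site still counts them in the residual variance, and its standard error is then too large. Site differences are plausible on the plan's own account: it calls delirium assessment subjective, and ICU staff carry it out. Baseline delirium subtype, Pre-Deliric score and age are already collected and likely to be prognostic, yet they enter only the supporting model. What is at stake is precision on the primary question.

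2. **The normality condition.** A condition with no stated test, threshold or replacement does not fix the primary method. Moving from a difference in means to a rank test would change the quantity estimated. If the data are already known not to be normal, the condition is an open door and not a safeguard.

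**Working it through.** **Inputs from the SAP article (Study methods):** "with an alpha value of 0.05 and a power of 80" per cent; "Superiority analyses will be two-sided and considered statistically significant at the 5% level"; mean 54, SD 45; target "detect a 10% increase in the percentage of delirium-free assessments", read as 10 percentage points; 425 per arm; up to 10% of patients never assessable.

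**Assumed:** the share of outcome variance explained by site and by covariates. The article gives neither, nor the number of sites, so ranges are shown.

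**Step 1: reproduce the plan's figure.** The standardised effect is 10/45 = 0.222. The two-sample t test at two-sided 5% and 80% power needs 318.8, so 319 per group, as stated. Then 319 × 1.15 = 366.9 (367) and 367 × 1.15 = 422.05 (423). The trial was sized for the unadjusted test, on the absolute reading of the 10% gain.

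**Step 2: effect of omitting site.** If site explains a share R² of the variance and allocation is balanced within site, the unadjusted SE is too large by 1/√(1 − R²), and the true size is 2 × [1 − Φ(1.96/√(1 − R²))].

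| Site R² (assumed) | SE too large by | 1.96/√(1 − R²) | True type I error |
|---|---|---|---|
| 0 | 0% | 1.960 | 5.0% |
| 0.01 | 0.5% | 1.970 | 4.9% |
| 0.05 | 2.6% | 2.011 | 4.4% |
| 0.10 | 5.4% | 2.066 | 3.9% |

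A simulation with 850 patients, blocks of 6 within 12 sites of about equal size (an assumption), a U-shaped outcome and 3,000 replicates agrees. With no site effect the t test's type I error is 0.050. At a site R² of 0.10 it is 0.039 unadjusted and 0.051 with site in the model. The Monte Carlo standard error is √(0.05 × 0.95/3000) = 0.004.

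**Step 3: effect of leaving out covariates.** Assessable patients: 425 × 0.90 = 382.5, taken as 382 per arm. The standardised effect becomes 0.222/√(1 − R²), where R² covers site and covariates together.

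| R² (assumed) | Effect/residual SD | Power, 382 per arm |
|---|---|---|
| 0 (unadjusted) | 0.222 | 86.6% |
| 0.10 | 0.234 | 89.9% |
| 0.20 | 0.248 | 92.9% |

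With the plan's 15% allowance taken off instead (425 × 0.85 = 361 per arm), unadjusted power is still 84.7%.

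**Step 4: can the outcome be normal?** On a 0–100 scale with mean 54, the largest possible SD is 100 × √(0.54 × 0.46) = 49.8. The audit variance is 0.45²/(0.54 × 0.46) = 0.2025/0.2484 = 82% of the maximum, so values must pile up at both ends. A normal curve with these moments would put Φ(−54/45) = 11.5% of patients below 0 and 1 − Φ(46/45) = 15.3% above 100, together 27% at impossible values. A beta distribution matched to the same moments, with parameters 0.122 and 0.104, puts about 36% of patients below 10%, 44% above 90% and 21% between.

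**The case against.** The strongest reply is that nothing here breaks the trial, and most of that stands.

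- **A reader might infer that the t test is invalid on such data, or that omitting site inflates false positives.** Neither follows. The plan's robustness statement is correct: the simulated type I error is 0.050 on a U-shaped outcome. Omitting site makes the test conservative. An unadjusted comparison is also unbiased under randomisation.
- **A reader might infer that the trial is underpowered.** It is not. Unadjusted power is 84.7% to 86.6% against a planned 80%, so adjustment adds to a surplus.
- **A reader might infer that the primary method will be chosen after unblinding.** The article does not say when normality is to be checked, and a pooled, blinded check would fit the text. It commits only to considering alternatives and gives a reason to keep the t test. What remains is that the alternatives are unnamed.
- **A reader might infer that every adjusted model excludes site.** Only the five-item list does so plainly. The supporting regression is not itemised, and the logistic and ventilation lists are open. The article also refers to additional files that are not shown.
- **The sizes rest on assumed R² values.** If site and covariates explain 1% or so, the gain almost vanishes.
- **Site fixed effects in every secondary model would go too far.** Polysomnography covers only a subset, and the logistic and ordinal mixed models could suffer from sparse sites.

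The 15% added for non-parametric data shows that non-normality was foreseen. It also hints that a rank test was in mind, so it does not settle what would replace the t test.

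**Conclusion.** The point holds as an improvement in precision and specification, not as a fault in validity. It is certain from the text that site is a stratification factor named in no model, that the primary test is unadjusted, and that the audit figures exclude normality. The cost of omitting site and covariates is modest and depends on the assumed R² values in the tables: a true size of 4.4% or 3.9% instead of 5%, and about 3 points of power at an R² of 0.10. It could be close to nil.

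The normality condition does not depend on those assumptions. It is bound to be met, the same sentence explains why it is unnecessary, and it leaves the replacement method and its estimand unspecified. That undercuts the article's stated aim of settling the analyses before results are known. This should be changed, but the unadjusted result would not mislead if it were not.

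**What to change.** Before database lock:

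1. **Primary analysis:** linear regression of each patient's percentage on treatment, site, age, gender, baseline delirium subtype (including none), diagnostic category and Pre-Deliric score, whatever the distribution. Report the mean difference with a 95% CI and robust standard errors.
2. **Practical rules:** state in advance how very small sites are pooled and how missing baseline covariates are handled. The Missing data section already provides for chained equations in variables other than the outcome; say that this applies here, or use a missing category.
3. **Supporting and sensitivity analyses:** keep the unadjusted t test as supporting. Delete the normality condition, and allow any rank test only as a sensitivity analysis.
4. **Secondary models:** add site to the adjusted models where numbers allow, as a fixed or random effect, or as strata in the Cox model. Do not force it into the polysomnography subset or into sparse models.

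The cost is SAP wording and the rules under item 2. The covariates are already needed for the supporting models, site is known from randomisation, and no larger sample is required.
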